### Questionnaires

The parents provide information about their socio-economic background and estimate the PA level of their children by questionnaire [using items from the Ballabeina study (Niederer et al., 2009)]. They will be asked for information about their children’s stress exposure and psychosomatic complaints. To assess stress exposure, a modified version of the 22-item Life Event Checklist (Johnson and McCutcheon, 1986) will be administered. The parents will report whether a specific event has occurred during the past 3 months and whether this event has negatively affected the well-being of the child from 1 (no effect at all) to 4 (strong adverse effect). As family issues are among the most important sources of distress among young children (Grant et al., 2003), family conflict will be assessed with the validated 9-item Conflict subscale of the Family Environment Scale (Moos, 1996). To assess their children’s mental health, parents will fill in the 8-item HBSC Symptom Checklist (Haugland and Wold, 2001). Additionally, parents will fill in the validated KINDL-R to assess children’s health-related quality of life (Ravens-Sieberer and Bullinger, 2004). Two validated questionnaires will be added to assess attention deficit hyperactivity disorder (Lidzba et al., 2013; Christiansen et al., 2016) and insomnia [lnsomnia Severity Index (Bastien et al., 2001)]. To eliminate language problems, the parental questionnaires will be translated from German in the other seven most spoken languages in Switzerland, i.e., French, Italian, Spanish, Portuguese, Serbian, Albanian, and Turkish (Statistisches Amt Basel-Stadt, 2010).

## Stepwise Procedures

### Study Design and Participants

The study will be conducted in a cohort of 6 to 8 year old children to assess the association of BP, body composition and PA and fitness with vascular, pulmonary, metabolic, autonomic and cognitive dysfunction as well as psychosocial health (Figure 1). The study is designed as a large-scale cross-sectional study. All primary school children of Basel-Stadt will take part in the measurements of motor skills and physical fitness, body composition and height during physical education lessons (*n* = ∼1000). Measurements will be conducted at every school in Basel-Stadt (*n* = 26). Children with an informed written consent by their parents will be allowed to participate in the medical screening on a separate visit. Approximately 1000 children with complete data will be included in the study (Figure 2).

**Figure 2 F2:**
[figure not shown]
Flow diagram.

### Setting

This cross-sectional study will be realized by the Department of Sport, Exercise and Health, Basel, Switzerland and will be conducted at all primary school in Basel-Stadt, Switzerland. The study has been approved by the Ethics Committee of Northwestern and Central Switzerland (EKNZ, No.: 258/12) and has been registered on ClinicalTrials.gov (NCT02853747).

### Study Procedures and Ethical Considerations

All children and their parents receive information authorized by the Ethics Committee of Northwestern and Central Switzerland (EKNZ) containing details on methods of the study. Only children with prior written consent from their parents are to participate. Children and parents will be briefed about their right to reject from the study without implications. On the day of the medical screening, children will be again asked to give their oral agreement. In between the medical screening, which will be scheduled to take 1 h per child, children will be distracted by the option of drawing with pencils and paper in a separated supervised play area. Children with a medical certificate that prohibits PA will be excluded from physical fitness assessment. All measurements conducted in this study will be non-invasive and performed according to standardized procedures for children. Retinal vessels will be analyzed by use of a non-mydriatic fundus camera. The use of eye-drops will not be required. The study will be carried out in accordance with the principles stated in the Declaration of Helsinki and the Guidelines of Good Clinical Practice (GCP) (World Medical, 2013). This study protocol was design according the SPIRIT Guidelines.

### Proposed Analysis

#### Statistical Analysis

Participants’ characteristics will be presented using descriptive statistics. Variance homogeneity will be assessed using Tukey-Anscombe Plots, and to assess normality, normal QQ plots of the residuals are to be used. To analyze our primary outcome, the associations of BP, BMI, and CRF with retinal arteriolar diameter (CRAE) in 6–8 year old school children, a multiple linear regression analysis using CRAE as outcome will be conducted. The regression models will be adjusted for age and sex as well as BMI and BP. To compare clinical categories of BP (normotension, prehypertension and hypertension) and BMI (normal weight, overweight, obesity), univariate analysis of covariance (ANCOVA) will be used. Pearson’s correlation will be used to assess the correlation of micro- and macrovascular parameters. Statistical analyses will be performed using the computer software program Stata 15 (StataCorp LP, Texas, TX, United States) and α < 0.05 will be considered as statistically significant. Arithmetic means and confidence interval (CI) will be calculated for each variable.

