### Potential Pitfalls

The medical screening will be conducted in school settings and not under laboratory conditions. The quality of the test procedures will be affected by the facilities available at the schools. To minimize confounding factors, test requirements and instructions during the test-period will be standardized assuring a high level of data quality. The medical screening and the fitness and motor skill assessments will be performed on separate days to allow for more comfortable timing and to ensure the measurements do not affect each other. On the day of the medical test, children are asked to remain fastened. They will receive a healthy small breakfast after the examinations. Each standardized measurement will be performed after at least 5 min of rest. In case of time restraints some children may not receive all of the measurements to remain within the scheduled screening time of 1 h per child and to ensure a high degree of data quality.

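### No planned analysis includes school, although children are measured on site at 26 schools; if exposure and CRAE both cluster by school, slope standard errors are too small and slopes may be confounded

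*Protocol article*

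**What the plan says.** Under Study Design and Participants, "Measurements will be conducted at every school in Basel-Stadt", with 26 schools given, and "Approximately 1000 children with complete data will be included in the study". Under Potential Pitfalls, "The medical screening will be conducted in school settings and not under laboratory conditions", and "The quality of the test procedures will be affected by the facilities available at the schools". The mitigation offered there is procedural: "test requirements and instructions during the test-period will be standardized assuring a high level of data quality".

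The Statistical Analysis section then fixes the methods. For the primary outcome, "a multiple linear regression analysis using CRAE as outcome will be conducted". On covariates, "The regression models will be adjusted for age and sex as well as BMI and BP". BP and BMI categories are compared by ANCOVA, and micro- and macrovascular measures are related by Pearson correlation. In addition, "Arithmetic means and confidence interval (CI) will be calculated for each variable". Residual plots are planned for equal variance and normality. School appears in none of these analyses, and the Sample Size Calculation makes no allowance for it.

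**The concern.** The regression, ANCOVA and correlation, as described, treat the children as independent. The protocol gives a reason to doubt this when it says that the place of testing affects the quality of the tests. Outcome and exposures share that place. CRAE and BP come from the screening held in schools, and CRF comes from a shuttle run on the school site during lessons (Physical Fitness section).

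Two things are at stake:

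- **Precision.** If exposure and outcome are both positively correlated within school, slope standard errors that ignore school are too small. P-values are then too small and confidence intervals too narrow.
- **Bias.** A school-level factor that shifts both an exposure and CRAE, such as testing conditions or social background, enters the BP, BMI and CRF slopes. Parents report socio-economic background (Questionnaires section), but the stated models contain neither it nor school.

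**Working it through.** **Inputs.** From the protocol: n of about 1000, 26 schools, α = 0.05, f² = 0.12 from the earlier cohort, and a stated power of up to 100% for an R² increment of 0.10 or more. Assumed: equal school sizes, five model terms, a two-sided test, and every ICC, since the documents give none.

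**Step 1: reproduce the stated power.** Noncentral F test for an R² increment, with λ = f²(u + v + 1), v = n − p − 1 and p = 5. An increment of 0.10 gives f² of at least 0.10/0.90 = 0.111. At n = 1000, power rounds to 1.000 for f² = 0.10, 0.111 and 0.12, whether u = 1, 2 or 5 terms are tested. The plan's figure is confirmed.

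**Step 2: design effect for a slope.** m = 1000/26 = 38.46. DE = 1 + (m − 1) × ICC(exposure) × ICC(outcome) = 1 + 37.46 × the product of the ICCs. True type I error = 2 × [1 − Φ(1.96/√DE)].

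| ICC exposure / outcome | DE | SE too small by factor | True type I error | Simulated, school ignored |
|---|---|---|---|---|
| 0.02 / 0.02 | 1.015 | 1.007 | 5.2% | 4.9% |
| 0.05 / 0.05 | 1.094 | 1.046 | 6.1% | 6.0% |
| 0.10 / 0.05 | 1.187 | 1.090 | 7.2% | 7.5% |
| 0.10 / 0.10 | 1.375 | 1.172 | 9.5% | 9.7% |
| 0.20 / 0.10 | 1.749 | 1.323 | 13.8% | 13.3% |

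The simulations used 26 schools of 38 or 39 children and 4000 runs per row. The third row was simulated with the two ICCs exchanged, which leaves their product unchanged. Cluster-robust standard errors, with a finite-cluster factor and a t reference on 25 degrees of freedom, gave 4.9% to 5.5% in the same runs.

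**Step 3: what this does to a result.** To reach a true 5% level, an estimate must exceed 1.96 × 1.172 = 2.30 naive standard errors in the fourth row, or 1.96 × 1.323 = 2.59 in the fifth. For BP at f² = 0.12, t is about √(0.12 × 1000) = 10.95. Even with DE = 1.749 it is 10.95/1.323 = 8.3. With f² = 0.111 and one tested term, power is still above 99.7% at an effective n of 211, the smallest examined.

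**Step 4: means.** If the 26 schools stand for a wider set of schools, DE = 1 + 37.46 × ICC. This is 1.75 at ICC 0.02 and 2.87 at ICC 0.05, so standard errors are too small by factors of 1.32 and 1.69.

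**The case against.** Several points on the other side stand.

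- **Schools are not sampled.** All primary schools in Basel-Stadt are included, and children enter the medical screening by individual parental consent. A reader might infer a cluster sample and conclude that nominal 95% intervals for means cover only about 86% to 75% (ICC 0.02 to 0.05). That holds only if inference extends to schools beyond these 26, and the protocol names no such target. For describing these schools' children, schools act more like strata.
- **The size is assumed.** No ICC is given, and at ICCs of 0.02 or less the effect on slopes is negligible. The wording on facilities could mean more noise or poorer images, not a common shift in CRAE. The standardized procedures may also keep school differences small.
- **The main BP result is safe.** A reader might infer that the power statement fails. Steps 1 and 3 show that it does not.
- **This is a condensed article.** The variance estimator could be left to a fuller analysis plan, and cluster-robust errors are compatible with multiple linear regression.

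The last point answers only part of the concern. The article does more than leave a detail open: it lists the covariates, and school is not among them. Robust errors alone would not remove between-school confounding, because they leave the slope unchanged. Nor does the inclusion of every school make children's residuals independent if they share rooms and equipment.

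**Conclusion.** The point holds conditionally. The stated analyses ignore a grouping that the protocol itself links to measurement quality. The direction of the error follows if exposure and CRAE are both positively correlated within school; its size cannot be derived from the documents. Over the assumed ICCs, true type I error for slopes runs from about 5.2% to 13.8%, and it departs materially from 5% only when the ICCs reach about 0.05 to 0.10. Possible confounding by school comes on top and cannot be quantified here.

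The claim that the primary error bars are certainly wrong is not supported. The power for an R² increment of 0.10 is unaffected. Weaker associations, for example with CRF or BMI, are where conclusions could change. Intervals for means are too narrow only for inference beyond the 26 schools. This should be fixed, but the study does not stand or fall on it.

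**What to change.** In the Statistical Analysis section:

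- Add school as a fixed effect to the regression and ANCOVA models. This removes between-school confounding, which a random intercept does only in part.
- Use cluster-robust standard errors with a small-sample correction for 26 clusters.
- Offer a random-intercept model as a sensitivity analysis.
- Compute the micro-/macrovascular correlations adjusted for school.
- Report the ICC of CRAE and of the main exposures.
- State whether the intervals for means describe these 26 schools or a wider population; in the second case, allow for clustering.

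The cost is a few lines of text and no new data, because each child's school is known and Stata 15 can fit these models. Confidence intervals become slightly wider, and the slopes must then be read as within-school associations.

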### Hypotheses

Hypothesis 1: BP and BMI are associated with retinal arteriolar narrowing, retinal venular widening and higher arteriolar stiffness.

Hypothesis 2: A higher CRF and PA level are associated with wider CRAE, narrower CRVE and lower arterial stiffness.

Hypothesis 3: High BP and BMI and low CRF/PA are associated with higher levels of AGEs, lower HRV, impaired pulmonary and cognitive function as well as adverse psychosocial health.

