### Pulse Wave Velocity (PWV)

Pulse wave velocity is a non-invasive and established measurement of arterial stiffness. Arterial stiffness is defined by the geometric and elastic properties of large arteries (Wassertheurer et al., 2010; Middeke, 2017). PWV will be examined using the validated oscillometric Mobil-O-Graph^®^ Monitor (I.E.M. GmbH, Germany) integrating ARCSolver software (Franssen and Imholz, 2010; Wassertheurer et al., 2010; Weiss et al., 2012). A slow PWV indicates low arterial stiffness. PWV will be calculated from the data of the pulse wave reflection and resembles an indirect measurement of central/aortic arterial stiffness. The oscillometric device estimates central systolic and diastolic BP and the cPP based on the measurement of the peripheral BP values. cPP resembles the systolic pressure maximum minus the diastolic pressure.

Pulse wave analysis will be performed in a supine position and appropriate small-sized cuffs are placed on the left upper arm. The first of two measurements will be taken after 5 min of rest to allow for calibration based on the systolic BP. Thereafter, two PWV measurements will be performed at 2-min intervals. After the measurements, data will be reviewed for quality and erroneous values according to the manufacture’s manual and as described previously (Wassertheurer et al., 2010). In case of poor data quality, further measurements will be performed to calculate the mean and standard deviation of at least two valid measurements.

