### Anthropometry

Standing height (without shoes) will be measured with a wall-mounted statiometer (Seca, Basel, Switzerland). Body weight and percentage body fat in light clothing will be measured using InBody 170, a bioelectrical impedance analyzer (InBody 170 Biospace device; InBody Co., Seoul, Korea). Based on recommendations of the American Heart Association, peripheral BP will be assessed after a rest period of 5 min at the bare right arm (Pickering et al., 2005). Children will be seated in a comfortable position in a quiet room. To reduce inter-observer variability, an automated oszillograph (Oscillomate, CAS Medical Systems, Branford, CT, United States) is used. Depending on the individual mid-upper arm circumference of the children, specific cuff-sizes for children will be fitted. BP measurements will be taken five times. For further analysis the mean of the three measurements with the smallest variation will be used (National High Blood Pressure Education Program Working Group, 2004). Central BP and the cPP will be measured by use of the oscillometric Mobil-O-Graph^®^ pulse wave reflection Monitor device as described above.

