It is a matter of ongoing debate, which non-invasive tissue biomarker best resembles underlying CV risk in age and disease. The study allows for the examination of pathophysiological links between the micro- and macrocirculation. So far, little is known about the cross-talk between the two vascular beds and how they influence one another. There is a need to examine early signs of vascular alterations and endothelial dysfunction in large as well as small arteries of the vascular bed. The retinal microcirculation is a new and innovative tissue biomarker for the assessment of CV risk and microvascular pathology in all age groups. On the basis of the current literature and our own preliminary work, it has been shown to be a valid and sensitive diagnostic tool to analyze underlying microvascular impairments in young children. Data on the association of physical fitness on micro- and macrovascular health and its interrelation with childhood health is scarce. Our study will increase our understanding of the complex mechanisms involved in the etiology and development of CVD.

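### The unadjusted micro-macrovascular Pearson correlation is confounded by BP, and the association of BP with central BP and cPP is built in

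*Protocol article*

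**What the plan says.** - **Micro-macro analysis** (Statistical Analysis): Pearson's "correlation will be used to assess the correlation of micro- and macrovascular parameters". No covariates are given for it. The adjustment for age, sex, BMI and BP is stated for the regression models only.
- **Central BP and cPP** (Pulse Wave Velocity): "The oscillometric device estimates central systolic and diastolic BP and the cPP based on the measurement of the peripheral BP values".
- **PWV** (same section): the first measurement is "taken after 5 min of rest to allow for calibration based on the systolic BP". On the calculation itself: "PWV will be calculated from the data of the pulse wave reflection and resembles an indirect measurement of central/aortic arterial stiffness". No equation is given.
- **Exposure BP** (Anthropometry): peripheral BP is taken seated on the right arm, where "an automated oszillograph (Oscillomate, CAS Medical Systems, Branford, CT, United States) is used". The pulse wave device is used supine on the left arm.
- **Expected directions** (Hypothesis 1): "BP and BMI are associated with retinal arteriolar narrowing, retinal venular widening and higher arteriolar stiffness". I read the last term as arterial stiffness, as in Aim 1.
- **Intended reading** (Discussion and Conclusion): "The study allows for the examination of pathophysiological links between the micro- and macrocirculation".

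The pitfalls, methodological considerations and general limitations do not mention that the macrovascular measures depend on BP.

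**The concern.** There are two separate issues.

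1. **Micro-macro correlation.** If BP narrows arterioles and goes with higher stiffness, as the study expects, CRAE and PWV will correlate even when neither vascular bed is linked to the other beyond BP. Age and sex can act in the same way. A raw Pearson coefficient mixes all of this. With 1000 children, even a weak induced correlation passes the 0.05 threshold, and the Discussion is set up to read it as a pathophysiological link.

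2. **BP against the central measures.** Central BP and cPP are outcomes, and BP is an exposure. The device derives the two outcomes from a peripheral BP reading, so an association with BP is expected from the method alone. For PWV the calibration on systolic BP makes some dependence possible. A BP-PWV association is then weaker support for the stiffness part of Hypothesis 1 than it appears.

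**Working it through.** **The plan's own figure first.** Sample Size Calculation states a power of up to 100% at n = 1000 for an R² increase of 0.10. Then f² = 0.10/0.90 = 0.111 and the noncentrality is f² × n = 111. The noncentral F test at 0.05 gives a power of 1.0000 with 1, 2 or 5 tested terms and up to 6 predictors. The quoted f² = 0.12 gives the same, and power is still above 0.99 at n = 300. The statement reproduces and is not in dispute.

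**Inputs for the induced correlation**
- r(BP,CRAE): from R² = 0.10, read as BP alone, |r| = √0.10 = 0.316. The sign is negative under Hypothesis 1. As a lower case, R² = 0.02 gives |r| = 0.141.
- r(BP,PWV): not in the documents. Assumed range 0.2 to 0.9.
- n = 1000; alpha 0.05, taken as two-sided.

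**Formula.** With no link beyond BP (partial correlation zero), r(CRAE,PWV) = r(BP,CRAE) × r(BP,PWV). The critical value at n = 1000 is |r| = tanh(1.96/√997) = 0.062. The chance of significance is taken from Fisher's z with standard error 1/√997.

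| Assumed r(BP,PWV) | Induced r, R² = 0.10 | Chance p < 0.05 | Induced r, R² = 0.02 | Chance p < 0.05 |
|---|---|---|---|---|
| 0.2 | -0.06 | 52% | -0.03 | 15% |
| 0.3 | -0.09 | 85% | -0.04 | 27% |
| 0.5 | -0.16 | 99.9% | -0.07 | 61% |
| 0.7 | -0.22 | >99.9% | -0.10 | 88% |
| 0.9 | -0.28 | >99.9% | -0.13 | 98% |

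For example, -0.316 × 0.5 = -0.158.

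**Check by simulation** (2000 runs, n = 1000, R² = 0.10, r(BP,PWV) = 0.3, 0.5 and 0.9). The raw correlation was significant in 84%, 99.95% and 100% of runs. After BP was partialled out, the mean correlation was about 0 and the rejection rate was 5.2% to 5.4%, as it should be.

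**Signs.** Under Hypothesis 1 the induced correlation with PWV is negative for CRAE and for AVR, and positive for CRVE.

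The contribution of age and sex was not quantified, because the documents give no figures for it.

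**The case against.** A reader might infer more: that both the BP-stiffness association and the micro-macro correlation will come out positive largely by construction. The documents do not support this, for four reasons.

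- **Sign.** The induced correlation is negative for the primary outcome CRAE and for AVR.
- **Mechanism.** Retinal diameters come from fundus images with no BP input. For the micro-macro correlation the problem is confounding by BP, not a shared computation.
- **PWV.** The article says only that central BP and cPP are estimated from peripheral BP. For PWV it mentions calibration and gives neither an algorithm nor a BP-PWV correlation, so a dominant BP component cannot be shown.
- **Separate readings.** Exposure BP comes from another device, arm and posture, so random measurement error is not shared.

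Other points on that side are also fair. The R² of 0.10 is the increment in the power statement, not an estimated BP-CRAE correlation. No aim or hypothesis formally tests micro-macro coupling, the macrovascular measures are listed as further outcomes, and the article disclaims causal inference. In a cross-sectional design BP may be a cause or a consequence of stiffness, so an adjusted coefficient can remove part of a real link. This tells against replacing the Pearson correlation.

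What remains is that the stated statistic has no adjustment, the study's own hypothesis makes BP a common correlate, and the stated limitations are silent on it. Choosing an unadjusted correlation while adjusting the regressions is a method fixed in the text, not a detail left open.

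**Conclusion.** The point holds in limited form. The association of BP with central BP and cPP is built in; for PWV it may be partly so. The micro-macro Pearson correlation is confounded by BP, age and sex and cannot by itself support a link between the vascular beds beyond BP.

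The size is uncertain, since it rests on the assumed BP-PWV correlation and on reading the R² as BP alone. It also assumes linear relations, a two-sided test and no clustering by school. Over most of the range examined, significance from BP alone is more likely than not. At the low end (R² = 0.02, BP-PWV correlation of 0.2) it is 15%, still about three times the nominal 5%.

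This concerns secondary analyses only.

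**What to change.** 1. Keep the raw Pearson correlation. Beside it, report a partial correlation, or a regression of CRAE, CRVE and AVR on PWV, adjusted for age, sex, BMI and the separately measured seated peripheral BP.
2. Rest any claim of a micro-macrovascular link beyond BP on the adjusted result.
3. Label BP versus central BP or cPP as descriptive, not as confirmation of a hypothesis.
4. Add a limitation that PWV may depend on BP through the calibration, and refer to it when interpreting the stiffness part of Hypothesis 1.

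**Cost.** Only analysis wording changes, because all the covariates are already collected. Under the directions the study expects, the adjusted correlation will be smaller. Because BP may lie on the pathway, adjustment may understate a real link, which is why both values should be shown.
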